
### Phase 2 (Completed)

#### Study Design

This study used a single-center feasibility and pilot randomized clinical trial with 3 arms. The study was registered on ClinicalTrials.gov (NCT04544618) on September 10, 2020 [57].

#### Overview

Phase 2 assessed the feasibility and preliminary outcomes of the VR OR prototype among patients undergoing breast cancer surgery. Specifically, with respect to the feasibility of this intervention, this study evaluated (1) recruitment capability and the characteristics of the resulting sample, (2) data collection procedures and selection of an appropriate outcome measure of PSA, and (3) participant acceptability and suitability of the VR OR intervention (ie, the active intervention) as well as the inclusion and acceptability of a VR control group (Nature Treks VR; ie, a non-OR immersive VR nature environment) and a TAU group. In addition, as a final aim, this study (4) pilot-tests the preliminary impact of the active intervention on PSA.

This study aimed to recruit 45 participants (n=15, 33% randomized to each arm [ie, active intervention, VR control, and TAU]). This target sample size is consistent with recommended guidelines for determining the sample size of a feasibility study and previous studies of this nature [58,59]. Furthermore, as an aim of this feasibility study, we are evaluating the extent to which we are able to recruit participants within the target population, which will inform modifications to the recruitment method as well as the expected duration of the upcoming randomized controlled trial (RCT).

#### Inclusion and Exclusion Criteria

The inclusion criteria for participation are as follows: (1) being aged ≥18 years, (2) able to speak and read English, (3) having a breast cancer diagnosis, and (4) scheduled or being scheduled to undergo breast cancer surgery under general anesthesia at the HSC. Those who do not meet these criteria, are not competent to provide informed consent (eg, due to cognitive impairment), or are unable to participate in a VR intervention (eg, due to significant visual or auditory impairments) are excluded.

#### Recruitment

Patients undergoing oncological surgery are recruited from the HSC via posters, patient surgical oncology appointment, or preoperative education class at the Shared Health Breast Health Centre (ie, a public health breast center that coordinates clinical assessment, diagnostic tests, treatment, education, and support) or the Breast & Gyne Cancer Centre of Hope (ie, resource center). A staff person or physician at the Breast Health Centre or Breast & Gyne Cancer Center of Hope (or research coordinator) briefly describes the study, and the contact information of interested patients is recorded. Recruitment posters with study staff’s contact information are posted at the Breast Health Centre, Breast & Gyne Cancer Center of Hope, the HSC, and on the web for any potential participants not identified at the time of their surgical oncology appointment or the preoperative education class.

#### Protocol

Phase 2 used a single-blind randomized design (1:1:1 randomization; stratified according to surgery type [with vs without reconstruction] and whether neoadjuvant chemotherapy was received; stratification enables equal proportions of participants with these characteristics across each of the 3 study groups), using quantitative and qualitative methodologies. This was done to assess the feasibility of, and pilot-test, the VR simulation to expose patients undergoing breast cancer surgery to the OR and induction process (ie, VR OR) compared to a non–surgery-related VR simulation (ie, VR control) and TAU. All participants complete self-report measures approximately 2 weeks before surgery (ie, baseline; for VR groups, this will occur on the day of the VR visit as well as before and after testing the intervention), on the day of surgery (preoperative period), 5 days after surgery (acute postoperative period), and 30 days after surgery (30-day postoperative follow-up).

Randomization is carried out using a web-based random number generator (details of how these random numbers are generated are available on the website) [60]. A master file was created in Excel (Microsoft Corp) by author JS, which consisted of 4 different stratification groups to correspond to the number of possible combinations: no chemotherapy and no reconstruction; no chemotherapy, with reconstruction; chemotherapy, no reconstruction; and chemotherapy and reconstruction. Using the web-based number generator, each stratification group was populated with equal proportions of the randomly ordered numbers (1, 2, or 3) that corresponded to the intervention groups to which a participant could be assigned (1: OR intervention; 2: Nature Treks VR intervention, and 3: TAU). Only research personnel who randomized the participants had access to the file. Due to the nature of this study, only partial blinding was possible. Specifically, those in the TAU group received no VR intervention, but those randomized to VR control versus the VR active intervention were blinded. Participants randomized to either the active intervention or VR control group schedule a meeting date to undergo the VR intervention, approximately 2 weeks before their surgery, during their telephone call with the study coordinator. On the day of the intervention meeting, participants complete baseline questionnaires before the intervention and additional questionnaires after the intervention (detailed in the *Measures* section). Those randomized to TAU are either emailed a link to complete the baseline measures using Qualtrics software (Qualtrics International Inc) or are mailed a hard copy, depending on their preference, 2 weeks before their surgery (baseline). On the day of surgery (preoperative period), participants again complete the measures assessing PSA that had been assessed at baseline. Five days after surgery (acute postoperative period), participants will complete the PSA measures, in addition to the other initial baseline measures. Finally, all baseline measures are readministered at the 30-day postoperative follow-up. For both postoperative follow-ups, participants have the option to receive hard copies of the measures via mail (to complete within 72 hours) or a survey link to complete the measures on the web.

For the active intervention group, the VR simulation begins with the patient sitting on a hospital bed, wearing the VR headset, and holding the controllers. The details of the final prototype are described in the *Phase 1 (Complete)* section and represented in Figure 2. For the exploration component, the patient is instructed to explore the VR OR for a minimum of 5 minutes, although the exploration period can last longer (the total duration engaged in the simulation is tracked for each participant). After the exploration period, the scripted portion of the simulation begins. As detailed previously, the simulation ends after the virtual oxygen mask is placed on the patient’s mouth, and the screen darkens. The scripted portion of the simulation is approximately 3 minutes long (ie, participants will spend a minimum of 8 minutes engaged in the VR intervention).

Participants randomized to the control intervention have the opportunity to explore a non–surgery-related VR simulation preprogrammed in the VR goggles (ie, Nature Treks VR experience). Participants are instructed to explore a selected nature environment for a minimum of 10 minutes, and their total duration engaged with the simulation is tracked. Participants in the TAU group receive the standard of care; they receive no additional intervention and have the option to receive information at their surgical oncology appointment and attend preoperative education classes, which all patients have the opportunity to attend. After the completion of the study, all participants are provided with a debriefing form that explains the purposes of the study.

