#### Data Analysis

Quantitative data will first be analyzed descriptively: the recruitment, engagement, and attrition rates will be calculated; sample characteristics will be summarized (both across the total sample and within each group); and mean scores on measures will be reported (within each group). The assessment of acceptability will be based on open-ended qualitative feedback regarding impressions of the VR intervention, which will be analyzed using content analysis with NVivo 12 (Lumivero), which was designed to assist with qualitative data organization. We will also determine acceptability based on the developed Likert scale questions. Means or medians will be reported depending on the distribution of the data. A triangulation approach will be used to amalgamate data sources and comprehensively assess acceptability. Paired samples *t* tests (1-tailed) and repeated measures ANOVAs will assess whether there are changes in participant-reported symptoms across the duration of the study within the active intervention group. If power permits, independent samples *t* tests (or an ANOVA, followed by post hoc pairwise comparisons) will assess whether there are mean differences in PSA scores between (1) the active and control intervention groups and (2) the active intervention group and TAU (this will be examined descriptively if underpowered). We will also examine changes in physiological arousal (an objective indicator of distress), assessed via skin conductance and heart rate, between and within (ie, during VR intervention vs within OR) intervention groups, and we will assess whether self-reported distress and anxiety scores are correlated with the indices of physiological arousal. Physiological data will also be integrated in the VR technological paper (in development) to understand whether physiological indices change during the VR experience (indicative of immersion). Finally, if power permits, independent samples *t* tests and ANOVAs will assess whether there are mean differences in patient-reported symptoms according to certain sample characteristics (eg, age, clinically significant anxiety, history of previous surgery, and type of surgery), both within the active intervention group and within the complete sample.

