### Limitations

The development of this research took place during the peak of the COVID-19 pandemic, and therefore, there were unanticipated recruitment challenges and overall delays in development. First, lockdown orders initially slowed the development and refinement of the VR OR prototype itself due to work-from-home orders. Once the prototype was completed, there were further issues due to surgery delays, along with advisories against *unnecessary* hospital visits, and changes to how patients were initially approached for their interest in participating (the Breast Health Centre changed the format of education classes from in-person to virtual sessions, and eventually some classes were canceled altogether). Ultimately, from December 2021 to December 2022, only 8 participants were recruited. Of note, during this time, there were also intermittent periods where no clinical research could be conducted. However, from January to September 2023, an additional 15 participants were recruited. This increase in recruitment may relate to changes in societal and health care practices (eg, vaccinations, reduced COVID-19 hospitalizations, and the removal of public health mandates) and will be explored further in the feasibility analysis.

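### The between-arm anxiety comparisons omit both stratification factors, and the list procedure described does not by itself assure the balance credited to stratification

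*Protocol article*

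**What the plan says.** The Protocol section of the article (Methods, Phase 2) describes "1:1:1 randomization; stratified according to surgery type", with and without reconstruction, and by receipt of neoadjuvant chemotherapy. It adds that "stratification enables equal proportions of participants with these characteristics across each of the 3 study groups".

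The same section then describes the list. A master file was made, "which consisted of 4 different stratification groups to correspond to the number of possible combinations", and "each stratification group was populated with equal proportions of the randomly ordered numbers (1, 2, or 3" standing for the three arms. No blocks, block size or list length are given.

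On size, the Overview states: "This study aimed to recruit 45 participants (n=15, 33% randomized to each arm". Limitations reports that "from December 2021 to December 2022, only 8 participants were recruited" and that "from January to September 2023, an additional 15 participants were recruited". Results says that the VR control arm was dropped, leaving two arms, and that recruitment ended in December 2023. The final number is not given.

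Data Analysis plans, if power allows, independent t tests ("or an ANOVA, followed by post hoc pairwise comparisons") for the active intervention against VR control and against treatment as usual, with a descriptive comparison otherwise. Neither stratification factor enters these comparisons. Type of surgery appears only later, as one example of a characteristic by which symptoms may be compared.

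**The concern.** There are two linked issues.

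**Analysis.** The design treats reconstruction and chemotherapy as worth controlling, but the named between-arm tests do not use them. If either factor is related to anxiety, a chance difference in its frequency between arms moves the estimated arm difference. If stratification did balance the factors, an unadjusted test leaves their variation in the residual and reports a standard error that is too large. Either way, information already recorded at randomisation is not used.

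**Balance statement.** Stratification alone does not equalise arms. It needs a restriction, such as blocks, that holds wherever a list happens to stop. A list with equal totals of each code guarantees equality only at its end. The later loss of one arm adds a gap, since the article does not say what happened to the entries coded for it.

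At stake is the reading of the preliminary between-arm trends, which the Limitations section says will add confidence in the intervention's potential utility. The feasibility outcomes are not affected.

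**Working it through.** **Inputs from the article.** Target 3 × 15 = 45, which reproduces the stated total. Recruited by September 2023: 8 + 15 = 23. Four strata. Three arms at the start, two after the amendment.

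**Inputs assumed, because the article does not give them.** Stratum shares equal (25% each) or skewed (50/20/20/10%); 24, 48 or 90 entries per stratum list; 23 people treated as all allocated in one design.

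**Step 1: what a part-used list does.** If n people draw from an unblocked list of L entries with a third for each arm, the number in one arm has variance n × (1/3)(2/3) × (L − n)/(L − 1). The last factor is the ratio to simple randomisation. With equal shares:

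- 45/4 ≈ 11 per stratum: 13/23 = 0.57 (L = 24), 37/47 = 0.79 (L = 48), 79/89 = 0.89 (L = 90).
- 23/4 ≈ 6 per stratum: 18/23 = 0.78, 42/47 = 0.89, 84/89 = 0.94.

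So a part-used unblocked list sits close to simple randomisation when the list is long or the stratum small.

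**Step 2: simulation (8,000 runs per setting).** Stratum counts are multinomial. Each stratum is allocated from one shuffled list or from permuted blocks (of 3 or 6 for three arms, 2 or 6 for two). The gap is the largest minus the smallest arm value; ranges run over shares and over list lengths or block sizes.

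| Setting | Quantity | Unblocked list | Blocks |
|---|---|---|---|
| 45, three arms | mean gap in arm size | 4.0–6.2 | 1.5–2.1 |
| 45, three arms | mean gap in reconstruction share | 15–21 points | 5–8 points |
| 45, three arms | chance that gap is 20 points or more | 26–49% | 0–1% |
| 23, three arms | mean gap in reconstruction share | 26–32 points | 11–16 points |
| 23, three arms | chance that gap is 20 points or more | 64–73% | 6–30% |
| 23, two arms | mean gap in reconstruction share | 14–17 points | 6–9 points |
| 23, two arms | chance that gap is 20 points or more | 25–35% | 0–7% |

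**Step 3: what a gap does to an unadjusted contrast.** If a factor shifts anxiety by d standard deviations and its share differs by g between arms, the contrast moves by g × d. The article gives no d; take 0.2 to 0.8 as an assumed range. For 23 people in two arms:

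- Unblocked: 0.14 × 0.2 = 0.03 to 0.17 × 0.8 = 0.14 SD.
- Blocked: 0.06 × 0.2 = 0.01 to 0.09 × 0.8 = 0.07 SD.

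The standard error of a 12 versus 11 comparison is √(1/12 + 1/11) = 0.42 SD. The typical shift is therefore at most about a third of one standard error (0.14/0.42).

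**Step 4: cost and gain of adjustment.** Residual degrees of freedom fall from 45 − 3 = 42 to 40, or from 23 − 2 = 21 to 19. If the two factors explained 10% or 20% of the variance (assumed), the residual SD would be multiplied by √0.90 = 0.95 or √0.80 = 0.89. If they explained none, the cost is the 2 degrees of freedom and a small loss from any imbalance.

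**The case against.** The best reply is that this is a feasibility trial described in a condensed article. Its primary measures concern feasibility, the between-arm tests are conditional on power, and the article concedes that it is underpowered. Block size and covariate lists are often left to a fuller protocol or analysis plan. An unadjusted t test is not invalid: chance imbalance is random error rather than systematic bias, and not crediting achieved balance tends to make the test conservative. All of this stands and limits the weight of the point. It does not remove it, because the article does name the tests, and the tests named leave both factors out.

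A reader might go further and infer four things that the documents do not support.

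- *That the lists were unblocked and stopped part-way, so balance failed.* The description also fits repeated random orderings of the three codes, which are blocks of 3. List length is not given, and achieved balance is not reported. The article says that stratification enables equality, not that equality was achieved.
- *That entries for the dropped arm were skipped.* The lists may have been regenerated. The amendment details are in an appendix that is not shown.
- *That the factors were chosen because they predict distress.* No reason for choosing them is given.
- *That the missing covariates are why balance is not delivered.* The analysis model has no bearing on how people were allocated; it is a separate issue.

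**Conclusion.** The firm part is the analysis: randomisation uses two factors, and the named between-arm comparisons use neither. Adjusting for them is a better method at a cost of 2 degrees of freedom.

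The balance part holds in a limited form. Equality across arms is not assured by the procedure as described, because that requires blocks or fully used lists and the article states neither. How large the shortfall might be is conditional. If the lists were unblocked, balance is materially worse than with blocks under every share and list length tried; if they were blocked, the concern largely disappears at 45. Even blocks leave some imbalance at 23 in three arms. Whether balance failed in this trial cannot be determined from the article.

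The overall consequence is modest: it touches exploratory contrasts only, and the typical shift, under the assumptions above, is well below one standard error.

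**What to change.** - **Analysis.** In Data Analysis, replace the independent t tests or ANOVA for the between-arm anxiety comparisons with a linear model (ANCOVA) containing arm, reconstruction (yes/no) and neoadjuvant chemotherapy (yes/no), as main effects only. This costs 2 degrees of freedom and no new data, since both factors were recorded at randomisation.
- **Reporting.** Give arm counts by stratum, so that the balance achieved can be seen. This also serves the descriptive fallback.
- **Wording.** In the Protocol section, say that stratification aims at balance on the two factors. State whether the lists were blocked and how allocation continued after the VR control arm was dropped.

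A change to the allocation scheme itself would come too late here, because recruitment ended in December 2023. The planned larger trial is to have its own protocol, which is the place to specify blocking.

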#### Measures

A variety of self-report measures are administered to participants across 4 time points of this study (ie, baseline or VR visit, preoperative period, acute postoperative period, and 30-day postoperative follow-up). Baseline measures are administered approximately 2 weeks before surgery (at the VR intervention visit for the intervention groups or via mail or web-based for the TAU group). These measures include a background sociodemographic questionnaire (eg, assessing age, marital status, diagnosis, type of surgery, previous history of surgeries, and mental health diagnoses); the Preoperative Intrusive Thoughts Inventory (PITI) [61]; the Amsterdam Preoperative Anxiety Information Scale (APAIS) [62]; the NCCN Distress Thermometer (a visual analog scale; also adapted for anxiety) [63,64]; the Peritraumatic Distress Inventory [65]; the Primary Care Screen for Posttraumatic Stress Disorder Diagnostic and Statistical Manual of Mental Disorders, Fifth Edition [66]; the Brief Resilient Coping Scale (BRCS) [67]; and the Patient-Reported Outcomes Measurement Information System (PROMIS) anxiety [68], depression [68], global health [69], fatigue [70], and emotional support scales [71]. The sociodemographic data collected were informed by the methodology used in a previous study by Grocott et al [72] that itself informed the current methodological approach. All mental health symptom scales are empirically validated self-report measures in various health populations, languages, and cultures. During the VR simulation, we also monitor participants’ skin conductance (using eSense Skin Response [Mindfield Biosystems Ltd]) and heart rate (using a Fitbit device [Google LLC]) while engaged in the VR simulation; participants are asked to report their level of distress and anxiety (using the NCCN Distress and Anxiety Thermometer scale ranging from 0 to 10) during the intervention (approximately 7 min from the start time). Throughout the simulation, research personnel complete a standardized behavioral observation form recording any notable verbal or nonverbal indications while in the intervention. After the simulation, the intervention groups complete the Igroup Presence Questionnaire [73] and a patient acceptability questionnaire (developed by the research team and including both closed-ended and open-ended items for participants to describe their impressions of the intervention). The patient acceptability questionnaire contains questions pertaining to rating the extent (on a scale ranging from 0% to 100%) to which the participant agrees to 13 statements about the VR intervention (eg, “I found the VR intervention was helpful” and “The VR intervention worsened my anxiety/concerns about my surgery”), open-ended and closed-ended questions about motion sickness, open-ended questions about what the participant liked and disliked and what they found helpful about the VR (if applicable), open-ended and closed-ended questions about whether the VR intervention was worthwhile, and a closed-ended question about other elements that should be included in the VR OR simulation.

On the day of surgery, all participants are asked to complete the PITI, the APAIS, and the NCCN Distress and Anxiety Thermometer either while they are in the waiting room or in the preoperative holding area (depending on when is most convenient and the timings of surgeries). Furthermore, we again monitor participants’ skin conductance and heart rate at this time. Participants are also asked to provide an additional rating for the NCCN Distress or Anxiety Thermometer while in the OR; instead of using the paper copy in the OR, the study coordinator or anesthesiologist asks participants to verbally indicate their current level of distress and anxiety (ie, on a scale ranging from 0 to 10). Five days after surgery, participants are asked to complete the NCCN Distress and Anxiety Thermometers; the PROMIS anxiety, depression, global health, fatigue, and pain intensity scales; a visual analog anxiety and distress graph; a postoperative summary form (to capture length of hospital stay and impressions of the various preoperative anxiety and distress measures); the BRCS; and the Peritraumatic Distress Inventory. Those in the active intervention group also receive open-ended questions requesting feedback to inform modifications that should be made to the second model of the simulation (in phase 3). Finally, 30 days after surgery, participants are asked to complete the NCCN Distress and Anxiety Thermometers; the PROMIS anxiety, depression, global health, fatigue, and pain intensity scales; the BRCS; and the Primary Care Screen for Posttraumatic Stress Disorder Diagnostic and Statistical Manual of Mental Disorders, Fifth Edition.

As will be detailed in the feasibility manuscript, although a number of self-report and objective measurements were obtained, the primary measures relate to feasibility (eg, recruitment and dropout rate as well as VR impressions and feedback). This feasibility study will also evaluate the extent to which these measures are completed as instructed and best represent PSA and whether preliminary trends support decreases in PSA across the study duration. The primary outcome measure for the larger future clinical trial will be determined based on this study. The proposed primary outcome measures of interest include the PITI, the APAIS, and the NCCN Distress and Anxiety Thermometers.

